### Hypothesis

A greater proportion of people with osteoarthritis of the knee that complete the OAKP will report clinically meaningful improvements in pain, knee function and quality of life, at 8 weeks, and 6 months compared to those who complete the ASMP.

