### Statistical Power

Power calculations are based on the achievement of a minimal clinically meaningful improvement [24]. With an alpha (1-tailed) of 0.05 and a sample size of 73 people in each group, this study will have power of 80% to show that the response rate for ASMP is at least as high as the response rate for OAKP. This assumes that the response rates for the ASMP and OAKP groups are equal (at 38.0%, the level of response achieved for the WOMAC function scale in our earlier RCT [10]), and that a difference of 20.0 points or less is unimportant and allows for 20% drop out.

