### Data Analysis

Data will be analysed in a blinded manner using SPSS v17 for Macintosh. Treatment groups will be examined for comparability at baseline using unpaired t-tests or Chi-squared test as appropriate. Main comparisons between treatment groups will be performed using an intention to treat analysis. For all subjects who complete the 6-month measurements, previous values will be carried forward to replace any interim missing values.

The proportion of participants achieving minimal clinically meaningful improvement in the health status, quality of life and pain will be computed for each group at each observation time. The effect of the treatment, in terms of the proportion showing minimal clinically meaningful improvement will be examined using Chi-square test. Separate analysis will be conducted for each of the outcome variables of interest.

Further, participants will be classified as overall responders or non-responders. A favourable response to treatment (responder) will be defined according to scenario D of the OMERACT-OARSI criteria [25]. That is, an improvement of ≥ 50% in pain or function and an absolute change of ≥ 20 points on a 100 point scale, OR an improvement of at least 2 of the following: An improvement of ≥ 20% and an absolute change of ≥ 10 in two of pain, function and global health. The proportion of participants achieving responder criteria will be computed for each group at each observation time. The effect of the treatment, in terms of the proportion of responders will be examined using Chi-square test.

Finally, repeated measures ANOVA will be used to examine the differences between groups over time. Statistical significance will be inferred at a 1-tailed p < 0.05. Results will not be adjusted for multiple comparisons as all outcomes of interest have been nominated a priori and such adjustment would likely render all findings of interest non-significant, despite their clinical importance [26]. Separate analysis will be conducted for each of the outcome variables of interest.

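### The trial is sized around a 20-point response difference it calls unimportant, but its hypothesis and tests never use that margin, so OAKP can be declared better from about 14 to 15.5 points

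*Protocol article*

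**What the plan says.** Three sections of the protocol article bear on this.

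- **Statistical Power.** The calculation starts "With an alpha (1-tailed) of 0.05 and a sample size of 73 people in each group" and claims "power of 80% to show that the response rate for ASMP is at least as high as the response rate for OAKP". It assumes both response rates are 38.0%, taken from the WOMAC function scale in an earlier trial. It adds that "a difference of 20.0 points or less is unimportant" and says that 20% drop-out is allowed for.
- **Hypothesis.** "A greater proportion of people with osteoarthritis of the knee that complete the OAKP will report clinically meaningful improvements" than those who complete the ASMP. No minimum difference is given.
- **Data Analysis.** For the proportions, "The effect of the treatment, in terms of the proportion showing minimal clinically meaningful improvement will be examined using Chi-square test". The OMERACT-OARSI responder proportions are handled the same way. After the sentence on repeated measures ANOVA comes the general rule: "Statistical significance will be inferred at a 1-tailed p < 0.05". The 20-point margin does not reappear, and no estimate or interval is set against it.

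**The concern.** The plan commits itself to a limit of importance for the difference in response rates, then reads the same kind of outcome by a rule that takes no account of it. An observed difference of, say, 15 points with 73 per arm would support the hypothesis under Data Analysis and would be unimportant under Statistical Power. The comparison for which the sample size was computed, the difference against 20 points, is never carried out.

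This matters because the Background section expects delivery by health professionals to cost more than lay delivery and gives that as the reason to establish whether it brings added benefit. The size of any OAKP advantage, and not only its sign, therefore decides what the trial means for planning. How to read a difference between the significance threshold and 20 points should be settled before data are seen.

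**Working it through.** **Inputs.** From Statistical Power: 73 per arm, one-tailed alpha 0.05, power 80%, 38% response in both arms, margin 20 points, 20% drop-out. From Data Analysis: chi-square test, one-tailed p < 0.05. Drop-out leaves 0.8 × 73 = 58.4, taken as 58 per arm.

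**1. Reproduce the plan's figure.** As a non-inferiority calculation,

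n = (1.645 + 0.842)² × 2 × 0.38 × 0.62 / 0.20² = 72.8, so 73 per arm.

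This matches, and it confirms that the 20 points are percentage points of response serving as a non-inferiority margin. The match is before any drop-out. Power is 80.1% with 73 analysed and 71.7% with 58. A superiority calculation for 38% against 58% gives 77 per arm one-sided, not 73.

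**2. Where significance starts.** A rough threshold is 1.645 × √(2 × 0.38 × 0.62 / n):

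- n = 73: SE 8.03 points, threshold 13.2 points.
- n = 58: SE 9.01 points, threshold 14.8 points.

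In whole patients, with the pooled (chi-square) standard error:

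- 38/73 v 28/73: difference 13.7 points, z = 0.137/0.0824 = 1.66, one-tailed p = 0.048. One responder fewer (37/73) gives z = 1.50, not significant.
- 31/58 v 22/58: difference 15.5 points, z = 0.155/0.0925 = 1.68, one-tailed p = 0.047.

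Smallest significant difference (points) by version of the test:

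| Test | 73 per arm | 58 per arm |
|---|---|---|
| One-tailed chi-square, uncorrected | 13.7 | 15.5 |
| One-tailed, continuity-corrected or Fisher | 15.1 | 17.2 |
| Two-sided chi-square, uncorrected | 16.4 | 19.0 |
| Two-sided, continuity-corrected | 17.8 | 20.7 |

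**3. How often a result falls in the gap.** Exact binomial enumeration, ASMP at 38%, uncorrected one-tailed test, one endpoint:

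| True difference | n per arm | Significant | Significant and observed difference ≤ 20 points |
|---|---|---|---|
| 10 points | 73 | 35.7% | 24.4% |
| 15 points | 73 | 59.8% | 32.1% |
| 10 points | 58 | 30.6% | 16.5% |
| 15 points | 58 | 51.7% | 21.7% |

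**4. Which interval matches the test.** For 38/73 v 28/73 the unpooled SE is 8.16 points.

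- 90%: 13.7 ± 1.645 × 8.16 = 0.3 to 27.1, which excludes 0 as the one-tailed 5% test does.
- 95%: 13.7 ± 1.96 × 8.16 = −2.3 to 29.7, which includes 0 and disagrees with the test.

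Under equal rates with 73 per arm, the chance that the upper limit lies below 20 points is about 80% for the 90% interval and about 70% for the 95% interval. Only the 90% level keeps the stated power.

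**The case against.** The strongest reply is that this is a symptom and not a separate defect: the 20 points are a non-inferiority margin, the hypothesis is one of superiority, and once the two are reconciled the figure either goes or becomes the test margin. That is right about the cause, and the point should be read that way. It does not remove the need to act, because changing the sample size alone would not help: a larger trial would lower the significance threshold and widen the gap.

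Other objections also stand in part.

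- A superiority test normally becomes significant below its design difference: 1.645/(1.645 + 0.842) = 66%, and 13.2/20 = 66%. That alone is no fault. What is particular here is that the plan labels differences up to 20 points unimportant.
- The one-tailed sentence follows the ANOVA sentence and gives no direction. Applying it to the chi-square tests, in favour of OAKP, is an inference from the Hypothesis section. Two-sided testing with 58 per arm leaves almost no gap, or none with a continuity correction.
- A reader might infer that the plan equates significance with an important advantage. It does not say so. Being detectably greater and lying within a tolerance margin can both be true, and in the Hypothesis section clinical meaningfulness describes each participant's improvement, not the gap between arms.
- A reader might also infer that the report would hide the size of the difference. Data Analysis says that the proportions will be computed for each group at each time, so they can be subtracted. What is not fixed is how that difference is read against the margin.

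**Conclusion.** The point holds as a failure to use the plan's own margin. Statistical Power commits to 20 points as unimportant, and the Hypothesis and Data Analysis sections decide on zero difference alone. On the one-tailed reading with ASMP near 38%, OAKP would be declared better from about 14 points (73 per arm analysed) or 15.5 points (58 per arm), or about 15 and 17 points with a continuity correction. All of these are inside the zone called unimportant.

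The figures rest on 38% response, which the plan takes from one scale and which may not hold for the other outcomes. They also rest on the test's direction and sidedness as inferred above. The documents do not support the stronger claim that the plan would report an unimportant difference as an important one. They support the narrower one: such a result can confirm the hypothesis, and nothing says how to reconcile it with the margin.

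**What to change.** In Data Analysis, report for each responder proportion the difference OAKP minus ASMP with a two-sided 90% confidence interval, and read it against both 0 and 20 points:

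- Lower limit above 20: OAKP better by an important amount.
- Lower limit above 0 but not above 20: OAKP better, important advantage not established. Note when the estimate is 20 points or less.
- Upper limit below 20: no important OAKP advantage. This may be stated alongside a lower limit above 0.
- Interval wholly below 0: ASMP better.
- Interval including 0 and reaching 20 or more: inconclusive.

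If the sponsor does not in fact regard up to 20 points as unimportant, withdraw or replace that figure in Statistical Power and restate what the 80% power refers to, so that the Hypothesis, Statistical Power and Data Analysis sections agree.

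The cost is a few sentences and one line of output per endpoint, with no extra patients or data. There are two downsides. A significant result with a difference of about 14 to 20 points can no longer be presented as a clear win for OAKP. Few results will establish an important advantage at this size: with 73 per arm and 71% v 38%, the SE is 7.8 points and the lower limit is 33 − 1.645 × 7.8 = 20.2, so an observed difference of about 33 points is needed.

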### Data Analysis

Data will be analysed in a blinded manner using SPSS v17 for Macintosh. Treatment groups will be examined for comparability at baseline using unpaired t-tests or Chi-squared test as appropriate. Main comparisons between treatment groups will be performed using an intention to treat analysis. For all subjects who complete the 6-month measurements, previous values will be carried forward to replace any interim missing values.

The proportion of participants achieving minimal clinically meaningful improvement in the health status, quality of life and pain will be computed for each group at each observation time. The effect of the treatment, in terms of the proportion showing minimal clinically meaningful improvement will be examined using Chi-square test. Separate analysis will be conducted for each of the outcome variables of interest.

Further, participants will be classified as overall responders or non-responders. A favourable response to treatment (responder) will be defined according to scenario D of the OMERACT-OARSI criteria [25]. That is, an improvement of ≥ 50% in pain or function and an absolute change of ≥ 20 points on a 100 point scale, OR an improvement of at least 2 of the following: An improvement of ≥ 20% and an absolute change of ≥ 10 in two of pain, function and global health. The proportion of participants achieving responder criteria will be computed for each group at each observation time. The effect of the treatment, in terms of the proportion of responders will be examined using Chi-square test.

Finally, repeated measures ANOVA will be used to examine the differences between groups over time. Statistical significance will be inferred at a 1-tailed p < 0.05. Results will not be adjusted for multiple comparisons as all outcomes of interest have been nominated a priori and such adjustment would likely render all findings of interest non-significant, despite their clinical importance [26]. Separate analysis will be conducted for each of the outcome variables of interest.

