#### Response to Intervention

Participants will be assessed using the following outcome measures at baseline (Week 1), immediately post-intervention (Week 8), and at 6 months after commencing the program. In addition, VAS pain will be assessed on a week-to-week basis during the first 8 weeks- that is the two assessment weeks and the 6 intervention weeks. A research assistant who will remain blind to group allocation will perform all assessments at all time-points. The primary outcomes for the study will be health status, quality of life and pain severity.

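### The analysis is labelled intention to treat, but its only missing-data rule covers 6-month completers and puts the baseline score into a missing Week 8 WOMAC or SF-36

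*Protocol article*

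**What the plan says.** All places are in the protocol article.

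- **Data Analysis** sets the population: "Main comparisons between treatment groups will be performed using an intention to treat analysis". The sentence after it is the article's only rule on missing data: "For all subjects who complete the 6-month measurements, previous values will be carried forward to replace any interim missing values".
- **Data Analysis** also says that the proportions with a meaningful improvement in health status, quality of life and pain "will be computed for each group at each observation time", and compares them by chi-square. For scores, "repeated measures ANOVA will be used to examine the differences between groups over time".
- **Response to Intervention** schedules the outcome measures at "baseline (Week 1), immediately post-intervention (Week 8), and at 6 months after commencing the program". Pain has an addition: "VAS pain will be assessed on a week-to-week basis during the first 8 weeks".
- **Hypothesis** is worded for completers, "A greater proportion of people with osteoarthritis of the knee that complete the OAKP" against the same proportion "compared to those who complete the ASMP", with 8 weeks and 6 months as the time points.
- **Statistical Power** takes 73 per group, a 38% response rate (WOMAC function in an earlier trial), a 20-point margin and 20% drop-out.

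**The concern.** There are two separate problems.

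**Drop-outs.** An intention-to-treat comparison needs some treatment of the outcome for everyone randomised. The rule given is limited to people who are measured at 6 months. It says nothing about those who are not, although the plan expects one in five to drop out. The completer wording of the hypothesis, and a repeated measures ANOVA that in its usual form needs complete cases, both point towards a completers analysis under an intention-to-treat label. If the choice stays open, it can be made after the data are seen.

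**Week 8.** For an outcome measured only at baseline, Week 8 and 6 months, the one interim value that can be missing is Week 8, and the one previous value is baseline. Carrying it forward sets change to zero, and zero change meets no improvement threshold. The observed 6-month score, which carries information on Week 8, is not used. Week 8 is a time point of the hypothesis.

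The bias can run either way. Equal missingness shrinks a true difference. That works against the hypothesis that OAKP does better, and in favour of the conclusion in Statistical Power that ASMP responds at least as well. Unequal missingness creates a difference where there is none.

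**Working it through.** **1. The plan's own figure.** Inputs from Statistical Power: p = 0.38 in both groups, margin 0.20, one-sided alpha 0.05, power 80%.

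n per group = 2 × 0.38 × 0.62 × (1.645 + 0.842)² / 0.20² = 72.83, so 73. Power at 73 is 80.1%. The figure is reproduced, but with nothing added for drop-out (73 / 0.8 = 91.25, so 92, would be needed). That is a separate point; here it means that losses come out of the 73.

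**2. How many have no rule.** 0.20 × 146 = 29.2, so about 29 participants; 0.80 × 73 = 58.4, so about 58 per group have 6-month data.

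**3. Why the handling matters.** Two readings fit the text, both at 20% loss in each group:

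| Reading | n per group | Response rate | Power, 20-point margin |
|---|---|---|---|
| Drop-outs excluded | 58 | 38% | 71.7% |
| Drop-outs kept as non-responders | 73 | 0.38 × 0.80 = 30.4% | 83.7% |

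Power = Φ(0.20 / √(2p(1−p)/n) − 1.645). First row: 0.20 / 0.0901 − 1.645 = 0.574. Second row: 0.20 / 0.0761 − 1.645 = 0.98.

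The extreme bounds are wide. Suppose 38% of those observed respond in each group. If all the unknown 20% respond in one group and none in the other, the rates are 0.304 + 0.20 = 50.4% and 30.4%. The 6-month difference can therefore move by up to 20 points in either direction, which is the whole margin.

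**4. Baseline carried into Week 8.** Let m be the share of an arm that misses Week 8 but is measured at 6 months. The documents give no value for m, so a range is assumed. It is also assumed that these people would have responded at the same rate as the others, and that 38% applies at Week 8.

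Reported rate = 0.38 × (1 − m). Reported difference = true difference × (1 − m), with the same m in both arms.

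| m | True 38% reported as | True 20 points reported as |
|---|---|---|
| 5% | 36.1% | 19 points |
| 10% | 34.2% | 18 points |
| 20% | 30.4% | 16 points |

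With equal true rates and unequal m, the false difference is 0.38 × (m₂ − m₁):

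- 5% v 15%: 0.38 × 0.10 = 3.8 points
- 0% v 20%: 0.38 × 0.20 = 7.6 points

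**5. Where step 4 applies.** It applies to WOMAC and SF-36 response at Week 8. VAS pain normally has a during-program score as its previous value, so its change is not fixed at zero unless the weekly scores are missing too. At 6 months, everyone to whom the rule applies has an observed value.

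**The case against.** The strongest reply is that an article may leave the handling of drop-outs to a statistical analysis plan, and that silence is not an error. That stands for silence alone. It does not cover a rule that the article does state, restricts to 6-month completers and sets directly after an intention-to-treat promise.

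Some stronger readings are tempting, but the documents do not support them:

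- **Drop-outs are excluded by rule.** A reader might infer this. The text does not say it, and a chi-square test that counts drop-outs as non-responders would also fit. Exclusion is the likely reading, no more.
- **People who leave an unhelpful program are removed from its denominator.** The rule turns on the 6-month measurements, not on attending sessions. Someone who leaves the course but is measured at 6 months stays in.
- **Every outcome is forced to non-response.** VAS pain has weekly scores. The performance tests have no responder definition in Data Analysis. Overall responder status can be met on pain alone, so if pain is taken from the VAS, a carried-forward WOMAC score does not settle it.
- **Losses produce a large spurious 6-month effect.** If 38% truly respond in both arms, all losses are non-responders and are excluded, and loss is 10% v 30%, the observed rates are 0.38/0.90 = 42.2% and 0.38/0.70 = 54.3%, a gap of 12 points. But the plan gives one drop-out figure and does not split it by arm. With equal 20% loss both arms show 0.38/0.80 = 47.5% and there is no spurious difference.

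It is also fair to object that imputation under missing at random does not cure outcome-dependent drop-out. For people with baseline data only, it would largely reproduce the completers' response rate. The remedy therefore needs sensitivity analyses.

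**Conclusion.** The concern holds in a limited form and should be fixed before analysis.

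The stated missing-data rule does not deliver the stated intention-to-treat analysis. It leaves about 29 of 146 participants without any handling at the plan's own 20% drop-out, and a completers analysis is the probable but unstated outcome. The two readings differ in power (71.7% v 83.7%), so the choice is not neutral.

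The Week 8 defect follows directly from the rule and the visit schedule. For WOMAC and SF-36 it lowers a 38% response by about 2 to 8 points for 5% to 20% missing. It creates a false difference of about 4 points at 5% v 15%. These sizes rest on assumed shares, on equal underlying response in those who miss the visit, and on 38% as the Week 8 rate. The direction for a given arm does not: forced non-response can only lower that arm's reported Week 8 response.

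The 6-month results are not touched by the carry-forward; their exposure is through the unhandled drop-outs.

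**What to change.** 1. Delete the carry-forward sentence in Data Analysis, and state that all randomised participants are analysed in the group to which they were allocated.
2. For scores, replace repeated measures ANOVA with a mixed model for repeated measures on all observed Week 8 and 6-month values, including those of people with no 6-month visit.
3. For response proportions, multiply impute missing follow-up scores within arm from baseline and the other follow-up visit, then derive response from the imputed scores.
4. As sensitivity analyses, count missing as non-response and run at least one missing-not-at-random scenario. Counting missing as non-response shrinks differences when losses are equal, so it is not a cautious choice for a claim that ASMP is no worse.
5. In Hypothesis, refer to people randomised to each program instead of people who complete it.

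The cost is changed wording and modest extra analysis work. No new data are needed.

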**Methods/Design:**

The effectiveness of the programs will be compared in a single-blind randomized study.

*Participants: *146 participants with established OA knee will be recruited. Volunteers with coexistent inflammatory joint disease or serious co-morbidities will be excluded.

*Interventions*: Participants will be randomised into either OAKP or ASMP groups and followed for 6 months.

*Measurements*: Assessments will be immediately before and after the intervention and at 6 months. Primary outcome measures will be WOMAC and SF-36 questionnaires and a VAS for pain. Secondary outcomes will include balance, tested using a timed single leg balance test and a timed step test and self-efficacy. Data will be analysed using repeated measures ANOVA.

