### Outcome measures

#### Western Ontario and McMaster Universities (WOMAC) Osteoarthritis index

WOMAC measures health status and assesses pain, stiffness and physical function in patients with OA of the hip or knee. For the purpose of this study the Likert (WOMAC LK3.0) format will be used. The WOMAC questionnaire is self-administered and can be completed in less than 10 minutes. Two major validity studies have shown WOMAC pain, stiffness and physical function subscales are valid and that the questionnaire is reliable and sensitive enough to detect changes in health status following a variety of interventions [13,14].

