#### The Short Form 36 Questionnaire (SF-36)

The SF-36 measures quality of life and has 8 sub-components reflecting both physical and mental status. It is comprised of 36 questions, is self-administered and can be completed in approximately 15 minutes. All estimates of score reliability, from 14 separate studies, for each of the 8 sub-categories of the SF-36 exceed accepted standards for measures used in group comparisons [15]. The SF-36 has been extensively validated in many English speaking countries of the world including Australia [16]. The rationale for using both WOMAC and the SF-36 for this study is that a combined approach using both generic and knee specific measures is considered likely to prove best for knee related problems [17].

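### Three co-primary instruments at two visits are each tested at an unadjusted 1-tailed 5% level, with no success rule and no consistent direction for the tail

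*Protocol article*

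**What the plan says.** The Abstract states: "Primary outcome measures will be WOMAC and SF-36 questionnaires and a VAS for pain". The section Response to Intervention gives the same three as domains: "The primary outcomes for the study will be health status, quality of life and pain severity". Neither place singles out a score or a visit. Two of the instruments have several parts. The WOMAC section says "WOMAC measures health status and assesses pain, stiffness and physical function in patients with OA of the hip or knee", and the SF-36 section says that the questionnaire "has 8 sub-components reflecting both physical and mental status".

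Data Analysis compares the proportion with a minimal clinically meaningful improvement by chi-square at each observation time, separately for each outcome variable. It adds chi-square tests of the OMERACT-OARSI responder and, last, repeated measures ANOVA. On the error rate it says "Statistical significance will be inferred at a 1-tailed p < 0.05" and "Results will not be adjusted for multiple comparisons as all outcomes of interest have been nominated a priori". It also argues that "such adjustment would likely render all findings of interest non-significant, despite their clinical importance".

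The Hypothesis predicts a larger proportion improved with OAKP, in pain, knee function and quality of life, at 8 weeks and 6 months. Statistical Power uses a 1-tailed 0.05 for a different statement: that the ASMP response rate is at least as high as the OAKP rate, within 20 points. It assumes 38.0% in both groups, "the level of response achieved for the WOMAC function scale in our earlier RCT".

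**The concern.** The article takes an explicit decision here, so this is not a detail left to an analysis plan. Neither of its two reasons supports the decision. Nominating outcomes beforehand stops investigators from choosing among results afterwards, but with several nominated outcomes and no success rule, any one of them can still be presented as confirming the hypothesis. That adjustment might remove significance is an argument for naming fewer primary comparisons. It is not an argument for leaving the error rate across them uncontrolled.

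The tail adds a second difficulty. A 1-tailed level means something only when the test has a direction and the direction is fixed. One of the planned tests has no direction, and for the others the document gives two.

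The Discussion says that the results will assist in planning self-management services, and the Background expects delivery by health professionals to cost more. A single unadjusted result among many could therefore be used to favour the costlier program.

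**Working it through.** **1. The plan's own figure.** Inputs from Statistical Power: 38% in both groups, margin 20 points, 1-tailed alpha 0.05, power 80%.

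n per group = 2 × 0.38 × 0.62 × (1.645 + 0.842)² / 0.20² = 72.8, rounded up to 73.

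The stated 73 reproduces (power 80.1%). It is a non-inferiority calculation, and it matches before any dropout is allowed for. WOMAC function supplies only the 38% rate; no comparison in the direction of the Hypothesis is powered.

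**2. Number of primary tests.** The document gives no count, so I bracket it.
- Narrow reading: 3 domains × 2 post-baseline visits = 6 chi-square tests.
- Subscale reading: (3 WOMAC + 8 SF-36 + 1 VAS) × 2 visits = 24 chi-square tests.
- The responder tests add 2 to either count. An ANOVA per outcome adds 3 or 12, giving 11 or 38 in all. I leave these out of the sizes below because they largely re-test the same outcomes.

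**3. Chance of at least one false positive when the programs do not differ.**

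If the tests are independent it is 1 − 0.95^k:
- k = 6: 1 − 0.735 = 26.5%
- k = 24: 1 − 0.292 = 70.8%

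The outcomes come from the same participants and will be correlated. The document gives no correlation, so the values of r are my assumption. I simulated k normal statistics with common correlation r (100,000 draws) and counted how often the largest exceeds 1.645, that is, one-sided tests all in the same direction.

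| Assumed r | 6 tests | 24 tests |
|---|---|---|
| 0.3 | 22.0% | 48.5% |
| 0.5 | 18.7% | 36.4% |
| 0.7 | 14.7% | 25.3% |
| 0.9 | 9.9% | 14.1% |

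**4. The tail.** With two groups and three assessments, the group-by-time test has (2 − 1) × (3 − 1) = 2 numerator degrees of freedom. It responds to any pattern of difference, so no 1-tailed version exists. The chi-square of two groups by improved or not has 1 df. Its signed square root is a z statistic, so it can be one-sided once a direction is fixed. The Hypothesis would reject when OAKP is better. The power statement would reject when ASMP is shown not to be worse by 20 points. These are different null hypotheses, with rejection on opposite sides.

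**5. Power at the planned 73 per group under a two-sided 5% level, before dropout.**
- Superiority, 38% against 58% (the 20-point difference taken as the effect). Pooled SE = √(2 × 0.48 × 0.52 / 73) = 0.0827. Unpooled SE = √((0.38 × 0.62 + 0.58 × 0.42) / 73) = 0.0810. Then (0.20 − 1.96 × 0.0827) / 0.0810 = 0.47, a power of 68.0%. The same comparison at 1-tailed 0.05 has 78.5%.
- Non-inferiority with the 20-point margin at 1-sided 0.025. SE = √(2 × 0.38 × 0.62 / 73) = 0.0803. Then 0.20 / 0.0803 − 1.96 = 0.53, a power of 70.2%.

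**The case against.** The best defence is that the Hypothesis reads as a conjunction: pain, function and quality of life, at both times. If all had to succeed, separate 5% tests would not inflate the error at all. Data Analysis does not adopt that rule, however. It tests each outcome on its own and defends non-adjustment on other grounds, so the conjunction cannot be taken as the plan.

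It can also be said that openly reporting unadjusted results, each with its own error rate, is a recognised position, and that the article cites a source for it. That is fair as far as it goes: a per-comparison 5% rate is stated. What is missing is any link between those separate tests and a single conclusion about the hypothesis.

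Four stronger readings are tempting, and the documents do not support them.
- That at least 24 primary tests are planned. The instrument sections describe subscales but do not say that each is a primary test; the named domains give 6. Use of the WOMAC function rate in the power section makes subscale testing plausible, not certain.
- That a false positive is likely. At 24 correlated tests in one direction the chance is below one half at every correlation tried, and with 6 tests it is at most 26.5%.
- That a 1-tailed chi-square is impossible. With 1 df it can be directed.
- That p-values will be halved whichever program looks better, which would double each test's error to 10%. The article does not say this, and the Hypothesis states a direction.

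**Conclusion.** The concern holds in this form: several primary outcomes at two visits, no primary score, visit or success rule, and an explicit refusal to adjust on grounds that do not control error. The familywise error is about 19% to 27% for 6 tests (correlation 0.5 to independence). If every subscale is tested it is about 25% to 49% at correlations of 0.7 to 0.3, and 70.8% under independence, which is implausible for these scales. Even at a correlation of 0.9 it is about double the nominal 5% or more. These sizes assume that any single success may be claimed, that the programs truly do not differ, and that all tests point the same way; the correlations are assumed.

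The 1-tailed level is inapplicable to the group-by-time F test. For the chi-square tests it is undefined until the Hypothesis and Statistical Power sections agree on a direction.

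**What to change.** 1. In the Abstract, Response to Intervention and Data Analysis, name one primary score and one visit. WOMAC function response at 6 months is one example, since the power section already uses that scale's response rate; the document itself fixes no visit. Make the other scales, the other visit, the OMERACT-OARSI responder and the ANOVA secondary, reported with 95% confidence intervals and not used on their own to confirm the hypothesis. Delete the argument that adjustment would remove significance.
2. Use two-sided p < 0.05 for the chi-square and F tests.
3. Reconcile the direction in the Hypothesis and Statistical Power sections, so that the power statement refers to the comparison that will be tested.
4. Restate power at the planned 73 per group: about 68% for 38% against 58% two-sided, or about 70% for the 20-point margin at 1-sided 0.025. Both are before dropout and fall further if participants are lost.

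This needs no new data or visits. The cost is fewer confirmatory outcomes and a stated power below 80%. Keeping 80% would take more participants before dropout: 97 per group for the superiority comparison or 93 for non-inferiority. Restating power at the planned size is the cheaper course.
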